# Paramedic Norwegian Acute Stroke Prehospital Project (ParaNASPP) study protocol: a stepped wedge randomised trial of stroke screening using the National Institutes of Health Stroke Scale in the ambulance

**DOI:** 10.1186/s13063-022-06006-4

**Published:** 2022-02-04

**Keywords:** Paramedic, Ambulance, Stroke, NIHSS, Triage, PPV, Mobile application

## Abstract

**Background:**

Less than 50% of stroke patients in Norway reach hospital within 4 h of symptom onset. Early prehospital identification of stroke and triage to the right level of care may result in more patients receiving acute treatment. Quality of communication between paramedics and the stroke centre directly affects prehospital on-scene time, emphasising this as a key factor to reduce prehospital delay. Prehospital stroke scales are developed for quick and easy identification of stroke, but have poor sensitivity and specificity compared to an in-hospital assessment with the National Institutes of Health Stroke Scale (NIHSS). The aim of the Paramedic Norwegian Acute Stroke Prehospital Project (ParaNASPP) is to assess whether a structured learning program, prehospital NIHSS and a mobile application facilitating communication with the stroke physician may improve triage of acute stroke patients.

**Methods:**

A stepped wedge cluster randomised controlled intervention design will be used in this trial in Oslo, Norway. Paramedics at five ambulance stations will enrol adult patients with suspected stroke within 24 h of symptom onset. All paramedics will begin in a control phase with standard procedures. Through an e-learning program and practical training, a random and sequential switch to the intervention phase takes place. A mobile application for NIHSS scoring, including vital patient information for treatment decisions, transferring data from paramedics to the on-call stroke physician at the Stroke Unit at Oslo University Hospital, will be provided for the intervention.

The primary outcome measure is positive predictive value (PPV) for prehospital identification of patients with acute stroke defined as the proportion of patients accepted for stroke evaluation and discharged with a final stroke diagnosis. One thousand three hundred patients provide a 50% surplus to the 808 patients needed for 80% power to detect a 10% increase in PPV.

**Discussion:**

Structured and digital communication using a common scale like NIHSS may result in increased probability for better identification of stroke patients and less stroke mimics delivered to a stroke team for acute diagnostics and treatment in our population.

**Trial registration:**

ClinicalTrials.govNCT04137874. Registered on October 24, 2019.

**Supplementary Information:**

The online version contains supplementary material available at 10.1186/s13063-022-06006-4.

## Background

Early identification of stroke symptoms and patient selection is an important factor for outcome and prognosis in acute stroke patients [1, 2]. Prehospital delay, time from onset to hospitalisation, may alone account for the largest proportion of total delay [3]. Less than 50% of stroke patients in Norway reach hospital within 4 h, which reduces the likelihood of successful acute treatment [4]. A unique feature of the Norwegian prehospital system is that all patients have to be conferred with an in-hospital doctor before hospitalisation. This means that all suspected stroke patients have to be conferred with a on-call doctor before arrival. Based on this prenotification the decision is made if the patient is to be assessed by the stroke team.

A combination of early prehospital identification of stroke, triage to the right level of care and improvement of in-hospital measures to reduce door-to-needle time may result in more patients receiving acute treatment [5]. Lower quality of communication between paramedics and stroke centre significantly increases prehospital on-scene time [6]. In a consensus statement from the European Academy of Neurology (EAN) and the European Stroke Organisation (ESO), training paramedics in recognising symptoms of all stroke types was strongly recommended [7].

National Institutes of Health Stroke Scale (NIHSS) is the most frequently used stroke scale to quantify stroke symptoms [8, 9]. It is composed of 11 items and higher scores indicate more severe strokes [8]. NIHSS has been introduced to the prehospital field and anaesthesiologists trained in prehospital critical care have shown to effectively assess NIHSS with good interrater agreement compared to an in-hospital stroke team physician [10].

Several shortened stroke scales have been developed for prehospital use, though with lower sensitivity and specificity compared to in-hospital assessment with NIHSS [11]. Prehospital scales may consequently fail to recognise stroke symptoms. Among these scales is the much used face arm speech time (FAST) scale, which is prevailing in prehospital procedures in Europe [12], Norway included. A recent study has suggested that FAST is insufficient for prehospital triage since large vessel occlusions (LVO) may be FAST negative [13]. In addition, FAST leads to too many false negatives in strokes with posterior circulation origin [14]. NIHSS also has a lower sensitivity for posterior strokes, but assessment for ataxia and visual field are important additions compared to FAST [15]. In contrast, another study found existing prehospital stroke scales to have acceptable diagnostic accuracy for identifying LVOs [16], though NIHSS is better, in comparison, at predicting LVOs [17]. However, a minority of stroke patients have LVOs [18]. A better stroke identification tool is thus recommended for prehospital providers [19]. By introducing the digital ParaNASPP platform with prehospital NIHSS we hope to establish a common language for stroke identification, standardise the prehospital assessment and provide a continuous evaluation through the chain of treatment.

An overtriage is currently necessary to achieve high treatment rates and is considered acceptable and cost-beneficial up to 30% [20, 21]. Further overtriage puts strain on both the pre- and in-hospital systems and delays correct treatment for stroke mimic conditions. In contrast, about a third of acute stroke patients are not identified in the prehospital setting [11, 19] which represents a highly problematic undertriage.

The study aims to explore whether ParaNASPP-trained paramedics using a mobile application with NIHSS and digital communication may improve triage of acute stroke patients and ensure standardised transfer of critical patient data to the in-hospital stroke physician. The intervention will be compared to paramedics using standard procedure with FAST and communication through regular channels. We hypothesise that the number of patients brought to the emergency department (ED) with suspected acute stroke and discharged with a stroke diagnose is significantly higher in the ParaNASPP model (intervention) compared to standard prehospital model (control).

## Methods and analysis

### Study setting

Emergency medical service (EMS) at Oslo University Hospital (OUH) in Norway consists of 15 ambulance stations with a total of 50 car ambulances staffed with two paramedics, one intensive care ambulance, six transport ambulances, four single paramedic units and one physician manned rapid response car without transport capability, and the helicopter emergency medical service (HEMS). Ambulance crews in Norway are a heterogenous group. In this paper, we use the term ‘paramedic’ regardless of education and experience. The total population of Oslo is approximately 700,000 inhabiting a 454-km^2^ area. Patient care in the area is split between OUH and three other hospitals, based on geographical and medical entities. OUH is the primary stroke centre in Oslo. All acute stroke assessment and treatment is carried out here. OUH receives stroke patients from an area and population covered by the five ambulance stations in the city, served by 21 paramedic staffed car ambulances. The study will take place in these five ambulance stations.

### Study design

The ParaNASPP study is a stepped wedge cluster randomised controlled intervention trial (SW-CRT). A SW-CRT is considered a pragmatic and robust study design [22] and suitable for prehospital research in an environment characterised by its complexity and inherent uncertainty [23]. Ambulance stations are natural clusters and a realistic approach for later implementation of the ParaNASPP model. For an overview of ParaNASPP see the SPIRIT figure (Fig. 1) and the SPIRIT checklist (Additional file 4) [24].

**Fig. 1 Fig1:**
[figure not shown]
Schedule of enrolment, intervention and assessment of ParaNASPP according to SPIRIT guidelines

All five ambulance stations in the city of Oslo are included in the study, each representing an individual cluster for patient recruitment. Between 250 and 300 paramedics working in these five clusters will participate in the study. After an initial 12-week period where all ambulance stations are in the control group, a random and sequential crossover of clusters from control to intervention will take place until all clusters are activated for intervention (Fig. 2). The clusters are activated only after successful completion of mandatory training, in 12-week intervals. For the last interval, all ambulance stations are enrolled in the intervention group. After 72 weeks patient inclusion is ended. The study will be completed after the final patient with a stroke diagnosis has had a 90-day follow-up.

**Fig. 2 Fig2:**
[figure not shown]
The ParaNASPP SW-CRT model

### Randomisation

The cluster randomisation is based on the sequential conversion of an ambulance station from control to intervention; hence, paramedics receive intervention training based on station affiliation. Cluster sequence is randomised, using a simple lottery draw, by the administration of the prehospital division. Five numbered notes were drawn randomly to select the order of the cluster activation. This is done independently and blinded from the research team.

### Study population

The inclusion criteria are met if a paramedic suspects acute stroke in a conscious, adult patient with stable vital signs. After an initial assessment, a focused medical history and physical examination is obtained. If the patient’s symptoms are compatible with acute stroke based on the clinical understanding of the paramedic, the on-call stroke physician will be contacted. Patients accepted to the OUH stroke team are formally included in the study. Written informed consent will be obtained from the patients or their next of kin for their anonymised participation in the study. If possible this is obtained during hospitalisation by members of staff at the Stroke Unit (SU), otherwise retrospectively by the research team (see Additional file 3). The ParaNASPP application (see Additional file 2) registers data every time it is used, also when the paramedic or stroke physician no longer suspects an acute stroke, but these patients are not included. Patients that are either pregnant, imprisoned or seen by a physician prior to ambulance transport to the hospital, will be excluded. Inclusion to the study depends on adherence to procedures. During the study period, there is a focus on information, team availability and follow-up to ensure study inclusion after protocol.

### The ParaNASPP model

Paramedics in the control and intervention clusters receive different levels of training. The intervention paramedics are trained in general stroke knowledge and assessment of acute stroke patients using NIHSS. NIHSS is scored using a mobile application that also provides direct communication through the application with the on-call stroke physician. The intervention comprises of NIHSS providing a standardised communication and an electronic transfer of data to the hospital upon arrival. In the control group, no specific training is provided. The mobile application is only used for the registration of suspected stroke patients, and the required conference with the on-call stroke physician is made by an ordinary telephone call.

### Preintervention training (intervention group)

The intervention consists of three parts: a theoretical electronic learning platform (ParaNASPP e-learning), standardised simulation training and an operative mobile application (the ParaNASPP application). Preintervention the paramedics have access to the e-learning for 3 weeks as part of the intervention. During this period, the cluster is still considered a control group. The decision to train the paramedics in NIHSS while still in the control group was made to keep the integrity of the intervention by ensuring only trained paramedics can use NIHSS in the application. They are instructed to maintain standard protocol until cluster activation. Knowledge obtained may still influence the way stroke patients are assessed, and for that reason, the time period for cluster training was kept as short as possible and we opened the application as soon as every paramedic in a cluster had received training in an effort to reduce the possible contamination of the data. The e-learning includes brain anatomy, stroke pathophysiology, in-hospital treatment options, NIHSS theoretical introduction and video-based training. All paramedics must complete the e-learning before the one-day simulation training of clinical assessment of acute stroke patients with the NIHSS. The course includes simulation scenarios of acute stroke symptoms scoring NIHSS using the application. The scenarios have a wide range of NIHSS scores and symptoms to mimic the spectrum of neurological deficits in acute stroke. The NIHSS simulation training is supervised by experienced stroke physicians and specially trained paramedics. Due to the ongoing COVID-19 pandemic and concern for spreading the infection, the preintervention training was converted to a digital format between activation of clusters three and four. The training content itself is identical for clusters before and during the pandemic, but the method for the practical day is changed. Before the pandemic, attendance was required for the practical training and simulation, and during the pandemic the practical training and simulation is digital and performed remotely using Teams (Microsoft’s chat-based collaboration platform, version 4.7.15.0). The digital training was tested before cluster activation, and the results will be published.

### ParaNASPP application

The ParaNASPP application is a mobile iOS application developed by the Norwegian Air Ambulance Technology. It is derived from a collaboration between neurologists, paramedics, researchers, graphic designers and app developers. The application was set out to digitalise the NIHSS assessment method and communication flow between the professionals, aiming to improve patient assessment and triage. It is a full-cycle solution including prehospital and in-hospital use, enabling ambulance car deployment, electronic medical record entry and securing data for scientific purposes. The application contains a full training module for digital learning and continued education of medical professionals. It keeps a high standard of engineering and security. The application is distributed through an enterprise master data management (MDM) solution to mobile devices in ambulances and hospitals. The access is limited to certified users only and uses a two-factor phone authentication and an employee-specific identification.

The application is installed on mobile phones of every participating ambulance, the on-call stroke physicians’ mobile phones and iPads in the SU and ED. Data collection prehospital is done by paramedics, in the ED by stroke physicians and by stroke nurses in the SU. All data registered in the application are automatically transferred to the University of Oslo, Services for sensitive data (TSD). The prehospital part of the application has both a control and an intervention version, with different functionalities (Table 1).

**Table 1 Tab1:** Functionality of ParaNASPP application

Application functionality	Control version	Intervention version	In-hospital version
Generation of study ID	X	X	
Registration of paramedic ID	X	X	
Ambulance trip ID (AMIS)	X	X	
Age	X	X	
Gender	X	X	
Onset of symptoms	X	X	
Delivery location	X	X	
COVID-19 status prehospital	X	X	
Antithrombotic medication		X	
NIHSS, individual elements and total score		X	X
Vital parameters registered—blood pressure, pulse rate, body temperature and blood glucose		X	X
Encrypted transfer of information to stroke physician via SMS		X	
Direct call through application to on-call stroke physician		X	
Generation of QR-code for transfer of data to in-hospital application		X	
QR-code scanner			X
Admission time			X
Time of imaging (CT, CTA, CTP, MRI			X
Time of IVT or EVT			X

*SMS* short message service, *CT* computer tomography, *CTA* CT angiography, *CTP* CT perfusion, *MRI* magnetic resonance imaging, *IVT* intravenous thrombolysis, *EVT* Endovascular thrombectomy

When assessing a patient with suspected stroke, the paramedics will enter their unique identification number into the application. Paramedics who have completed the ParaNASPP training and are part of an active intervention cluster will get access to the registration of prehospital NIHSS. This ensures that only ParaNASPP-trained paramedics may include patient data in the intervention group. An unregistered identification number will open the control version. Each use of the application generates a unique, anonymous study ID. It will only be possible to identify the person behind the study ID through a key stored on a separate computer at OUH, thus ensuring confidentiality. Additional file 1 displays the differences in the two prehospital versions.

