### ParaNASPP application (control group)

Paramedics in the control group access the control version of the application. An inclusion with this version registers suspected stroke cases. Patient assessment and communication with the on-call stroke physician are in agreement with standard procedure. This procedure entails FAST as a screening tool and communication with the on-call stroke physician through a direct telephone number. Figure 4 describes the patient flow and data collection in both control- and intervention groups.

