### Sample size calculation

Local registry data suggest that around 40% of patients admitted with stroke symptoms to the ED at OUH have a stroke diagnosis at discharge (700 stroke diagnoses out of 1800 admitted with suspected stroke during 2017 (unpublished data)). The prehospital pathway is not specified in the historical data. We aim for a 10% increase in the proportion of patients with a stroke diagnosis at discharge.

We used a two-sided test with alpha 5% and beta 80% and need a total of 808 patients to reach statistical significance. Due to the challenges of prehospital research in terms of large natural variation and loss to follow-up, we aim for a 50% patient surplus and intend to include 1300 patients. We estimate a 72-week study period to be sufficient to reach our goal. With all five stations including control patients before a stepwise cross-over to intervention, we end up with six 12-week periods. After the last cross-over, all paramedics have received training in the ParaNASPP model, and inclusion to the control group ends at this point. The study will be terminated after 72 weeks regardless of the number of patients included in the two groups.

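### The app's access rule sends patients of untrained or unregistered crews at activated stations to the control group, so grouping can depart from the randomised station and date

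*Protocol article*

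**What the plan says.** All references are to the protocol article.

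- **What is randomised** (Randomisation): "The cluster randomisation is based on the sequential conversion of an ambulance station from control to intervention". Paramedics are trained according to the station they belong to.
- **Who gets the intervention version** (ParaNASPP application): "Paramedics who have completed the ParaNASPP training and are part of an active intervention cluster will get access to the registration of prehospital NIHSS". The stated purpose follows: "This ensures that only ParaNASPP-trained paramedics may include patient data in the intervention group".
- **Everyone else** (same section): "An unregistered identification number will open the control version". No exception is made for activated stations, and no date limit is given.
- **What a control-version entry is** (ParaNASPP application, control group): "An inclusion with this version registers suspected stroke cases".
- **When stations are activated** (Study design): "The clusters are activated only after successful completion of mandatory training, in 12-week intervals". The section on preintervention training adds: "we opened the application as soon as every paramedic in a cluster had received training".
- **When control recruitment stops** (Sample size calculation): after the last cross-over all paramedics are trained, and "inclusion to the control group ends at this point".
- **How groups are compared** (Statistics): PPV is compared primarily on all included patients. Hierarchical models that allow for the timing of inclusion are only to be explored.

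**The concern.** The order of station conversion is the only random element in this trial. It protects the comparison if a patient's group is fixed by the station and the date. The access rule adds a second, person-level condition that is not randomised.

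Where an untrained or unregistered crew member works at an activated station, the patient is entered through the control version. Three things follow if that entry also sets the analysis group:

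- The intervention group is limited to trained, registered crews, while the control group before activation includes all crews. That is selection after randomisation.
- Patients from later calendar periods are added to the control proportion, and the crude primary comparison makes no adjustment for this.
- Control patients could still arise after the last cross-over, which sits uneasily with the statement that control inclusion has ended by then.

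A registered paramedic working at a station not yet activated might also open the intervention version, because access follows the ID. The protocol does not describe such shifts, so this is an inference.

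**Working it through.** **1. Which rule sets the group?** Two descriptions stand side by side.

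- By cluster and period: Study design speaks of whole stations being in the control or the intervention group, and the preintervention training section treats a cluster in training as still control.
- By person: the ParaNASPP application section ties entry into the intervention group to the paramedic's ID. In-hospital procedure describes intervention patients as arriving with a QR code, and Table 1 shows that only the intervention version generates one. Background describes the contrast as trained paramedics against paramedics on standard procedure.

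The two agree when every crew member at an activated station is trained and registered, and every registered member works at the home station. They disagree otherwise. The article does not say which one prevails.

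**2. The target effect.** The plan has no figure for cross-classified patients, so there is none to reproduce. The target effect can be confirmed from the sample size of 808. A two-sided 5% test of 40% against 50% with 80% power and continuity correction needs 408 per group, 816 in total; starting from 700/1800 it needs 812. A relative 10% increase (40% to 44%) would need 4,778 without correction. The target is therefore 10 percentage points.

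**3. Illustration with no true effect.** Inputs:

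- From the plan: 1300 patients, five stations, six periods, PPV about 40%. Control station-periods are 5+4+3+2+1+0 = 15 of 30, so equal recruitment per station-period gives 650 and 650.
- Assumed: a share m of activated-period patients enters through the control version; those crews have a PPV lower by s; the crew mix is the same before activation; there is no time trend.

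With overall PPV p, trained crews have q = p + ms and the others u = q − s.

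- Intervention by app version: q
- Control by app version: (650p + 650m·u) / (650(1+m))
- Difference: 2ms/(1+m)

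Example with m = 10%, s = 10 points: q = 41%, u = 31%, control = (260 + 20.15)/715 = 39.2%, difference 1.8 points.

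| Share m | Patients (of 650) | s = 5 | s = 10 | s = 20 |
|---|---|---|---|---|
| 5% | about 33 | 0.5 | 1.0 | 1.9 |
| 10% | 65 | 0.9 | 1.8 | 3.6 |
| 20% | 130 | 1.7 | 3.3 | 6.7 |

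Entries are spurious differences in points. With s = 0 they are all zero, and with s negative they change sign. With m = 1% and s = 10 the result is 0.002/1.01, about 0.2 points. Grouping by station and date gives zero throughout.

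**4. Cost of grouping by station and date.** If the true effect is +10 points in trained crews only, the station-and-date difference is 10(1−m): 9.5, 9.0 and 8.0 points for m = 5%, 10% and 20%. Power with 650 per group is 93.2%, 90.5% and 82.9%, against 95.3% with m = 0. Clustering is ignored in these figures.

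**The case against.** The strongest reply is that the access rule already contains the randomised status. Being part of an active cluster is one of its two conditions, so app version largely tracks the schedule. This stands. A reader might infer that grouping ignores the randomised station and date altogether; the text does not support that.

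Second, stations are activated only after training is complete, and the app was opened once every paramedic in the cluster had been trained. This also stands, and it suggests a small share. It describes the moment of opening, however. It does not cover anyone who joins or covers shifts later, and recruitment ran from June 2019 to July 2021 with a pause of almost seven months (Trial status). The article does not mention relief or new staff, so their presence is inferred, although a default for unregistered IDs provides for such users.

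Third, an access rule is not an analysis-set definition, and the statistical analysis plan, which is not shown, may define the groups by station and date. This stands in part. A reader might infer that the protocol commits to an as-treated primary analysis, but the article never says so. What it does state is a rule about who may contribute patients to the intervention group, and that goes beyond software access.

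Fourth, the statement that control inclusion ends at the last cross-over can be read as closing the control group whatever the software does. That is a fair reading. It would settle the last period only, not the earlier ones.

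Finally, a reader might infer a bias of 1 to 3 points in favour of the intervention. The article supports neither the share nor the lower PPV behind that figure, and it does not say that unregistered crews perform worse.

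**Conclusion.** The point holds in a limited form. The stated access rule follows the randomised schedule for most patients. It departs from it for untrained or unregistered crews at activated stations and possibly, by inference, for registered staff away from their own station. If it is applied as the grouping rule in the crude comparison, those patients are selected into control by crew characteristics after randomisation.

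The size and sign of the effect are unknown. The range of about 1 to 3 points, against a 10-point target, rests on an assumed share of 5% to 20% and an assumed PPV gap of 10 points. The training statements make a smaller share plausible. The point should be fixed because the correction protects the only randomisation and costs little, not because a material bias has been shown.

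**What to change.** - Define the primary exposure as the randomised status of the station on the date of the call, whichever app version was opened. State that control-version records from activated stations count as intervention, and the converse.
- Choose one rule for the station, either that of the ambulance or that to which the paramedic belongs, and use it throughout. Table 1 does not list station, so it must be linked from the trip ID and paramedic ID, which both prehospital versions record. The article does not confirm that the trip ID yields the station, so this link needs checking.
- Report the number of cross-classified patients by station and period.
- Keep app version as a measure of fidelity and for an as-treated sensitivity analysis.
- Reconcile the ParaNASPP application section with Study design, Preintervention training and Sample size calculation, including what happens to control-version entries after the last cross-over.

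The cost is one derived variable, the record linkage and a few sentences. The downside is some dilution of the effect by non-adherence, which should be reported with the result.
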